**9.7 Concomitant medications**

All concomitant medications will be reported on the appropriate case report form. In addition to prescribed and over-the-counter medications, methadone, vitamins, herbal remedies, and other ingested or inhaled traditional preparations will be recorded. Medications used for the treatment of adverse events (AEs) that occur during study participation will also be recorded on applicable study case report forms.

**10. Study visit summary (see Table 2 for details of each visit)**

**10.1 Screening visit**

At the screening visit, study staff will provide potential participants introductory information about the study. Those agreeing to participate will be given a screening ID number and a screening interview will be conducted. Study staff will provide a full description of the trial and procedures. Those who complete the screening and meet initial eligibility criteria will be given an appointment to review laboratory test results and final eligibility criteria.

**10.2 Enrollment visit**

Study staff will review inclusion and exclusion criteria with potential participants to determine trial eligibility. Those eligible will be assigned an enrollment ID number and appointments for the duration of study will be scheduled. Hepatitis B vaccination series will be initiated for hepatitis B seronegative participants.

**10.3 Follow-up visits**

Frequent follow-up visits will be conducted in order to:

1. Encourage adherence
2. Monitor symptoms, toxicities, and adverse events
3. Determine when HIV infection occurred as precisely as possible
4. Reduce the duration of monotherapy for those who become HIV-infected to limit development of antiretroviral drug resistance
5. Reduce recall bias in measures of adherence and HIV associated risk behavior

**10.3.1 Daily directly observed therapy (DOT)**

Participants will come to clinic each day and clinic staff will observe the participant swallow one tablet of tenofovir or placebo. Clinic staff will complete and sign the participant’s adherence card.

**10.3.2 Monthly visits (scheduled at 4 week intervals)**

Study staff will provide counseling, review study drug adherence, assess and record adverse event/s, do HIV and pregnancy tests, and collect/count unused medication and dispense a new supply. Participants will complete an adherence assessment questionnaire using an audio computer assisted self interview (ACASI).

**10.3.3 First two monthly visits and three monthly visits (weeks 4, 8, 12, 24, 36, etc.)**

Clinic staff will conduct all the monthly procedures. In addition, blood will be collected for laboratory testing. Participants will complete a risk behavior questionnaire using an ACASI at weeks 12, 24, 36, etc.

**10.3.4 Exit visit (Study completion, HIV infection confirmation visit, early termination)**

Clinic staff will conduct all the monthly and 3-monthly procedures. In addition, a blood specimen will be collected and a physical examination done.

**10.3.5 Follow-up visits for newly HIV infected participants**

All newly HIV infected participants will be followed at 4 weeks, 8 weeks, and every 16 weeks (4 months) after confirmation of HIV infection until the study ends. Participants will receive counseling, have a pregnancy test (women), and blood will be collected for laboratory testing. Participants will complete a risk behavior questionnaire using an ACASI at the 16 week (4 month) visits.

## Table 2. Bangkok Tenofovir Study Procedures Flow Chart

| **Procedures** | **Screening** | **Enrollment** | **Daily visit** | **Monthly visit** | **3 monthly visit** | **Exit visit** | **Post-analysis**  **monthly visits** | **Post-analysis**  **3-monthly visits** |
| --- | --- | --- | --- | --- | --- | --- | --- | --- |
| Screening informed consent | X |  |  |  |  |  |  |  |
| Screening questionnaire | X |  |  |  |  |  |  |  |
| Comprehension test |  | X |  |  |  |  |  |  |
| Physical exam1 |  | X |  |  |  | X |  |  |
| Enrollment eligibility |  | X |  |  |  |  |  |  |
| Enrollment informed consent |  | X |  |  |  |  |  |  |
| HIV pre/post-test counseling | X | X |  | X | X | X | X | X |
| OraQuick HIV testing | X | X |  | X | X | X | X | X |
| Urine pregnancy test (females) | X | X |  | X | X | X | X | X |
| HBV serology | X |  |  |  |  |  |  |  |
| Collect blood | X |  |  | M1 and M2 | X | X |  | X |
| Pill Count |  |  |  | X | X | X | X | X |
| Dispense 30 day supply of study medication |  | X |  | X | X |  |  |  |
| Review adherence diary |  |  | X | X | X | X |  |  |
| Adherence questionnaire (ACASI) |  |  |  | X | X | X |  |  |
| Adherence counseling |  | X |  | X | X | X | X | X |
| Risk assessment questionnaire (ACASI) |  | X |  |  | X | X |  | X |
| Risk reduction counseling | X | X |  | X | X | X | X | X |
| Update locator information | X | X |  | X | X | X |  |  |

1. A complete physical exam will be completed at enrollment and exit visits; a focused physical exam for specific participant complaints will be completed at other visits.

**10.3.6 Unscheduled visits**

Participants will be instructed to return to the clinic (without an appointment) as soon as possible if they experience symptoms or illness that may be related to study medication, upon release from a correctional facility if they have missed an appointment, if they no longer have access to study medication, or are unable to take study medication.

**10.3.7 HIV and additional testing in scheduled and exit visits**

If OraQuick test of oral fluid is non-reactive, the participant will be informed that there is no evidence of HIV infection. In order to ensure that daily oral tenofovir does not lead to OraQuick non-reactive test results among HIV-infected volunteers, HIV confirmatory nucleic acid testing (NAT) will be done on sera available from volunteers who test OraQuick non-reactive.

If OraQuick HIV testing is reactive, study medication will be stopped, and the participant will be informed that the test is reactive and that blood tests are required to confirm the result. If the participant agrees**,** blood will be drawn and confirmatory testing done (i.e., EIA and, if necessary Western Blot) and the participant will complete the risk assessment and adherence questionnaire.

At the follow-up visit in 2 weeks, participants will receive post-test counseling and results of confirmatory testing. Participants, who test positive on confirmatory HIV testing, will have HIV-1 viral load, HIV-1 genetic characterization, antiretroviral drug resistance and CD4 testing and will be referred for follow-up care. Participant specimens from previous visits will be tested to determine if the participant was in the HIV window period when they previously tested HIV negative by oral fluid testing.

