**14.2 Safety monitoring plan**

The Principal Investigator is responsible for continuous close monitoring of all AEs that occur among study participants, and for alerting study staff if unexpected concerns arise. The DSMB will have members from Botswana, Thailand, and the United States (sites of CDC supported tenofovir HIV prophylaxis trials). Members will be selected based on demonstrated expertise in statistics, medical ethics, epidemiology, behavioral science, medical care of HIV-infected individuals, and clinical research experience. The DSMB will be responsible for periodic (or emergency) review of safety data, and decisions about holding accrual or administration of study product for safety concerns.

Prior to initiation of the trial a data safety monitoring plan will be written and agreement about the plan reached with the DSMB. It will include at least the following:

- Specification of the adverse event detection and reporting system
- Content of interim data reports
- Frequency of interim data reviews
- Statistical methods for interim analyses
- Specification of safety and efficacy stopping rules
- Distribution of interim review reports

Interim reports will include at least the following information, by treatment arm, gender and age:

- Number randomized
- Number and timing of missed visits and drop-outs, accumulated follow-up time
- Baseline characteristics of study population
- Medication adherence
- Protocol violations, including ineligible persons enrolled, number who received an unassigned treatment, instances of unblinding
- Safety and efficacy outcomes
- number, percent, and rate of occurrence of primary outcomes
- number, percent, and rate of occurrence of secondary outcomes
- line listing of adverse events

Interim reports will also include:

- Multivariate analyses of outcomes adjusted for baseline differences between arms/strata
- Analyses of efficacy outcomes adjusted for medication adherence

At predetermined review intervals, the board will be convened (in person or by phone) to review the data provided and make a recommendation about:

- - Whether sufficient safety is demonstrated in the phase II trial to proceed to phase III
  - Whether safety and efficacy interim data indicate the continuation, revision, or discontinuation of the phase III trial

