**Appendix E. HIV testing algorithm**

Collect Oral fluid specimen

OraQuick

Give same-day result in clinic

non-reactive

Collect blood and make appointment for participant to return for result in 1 week

reactive

Send blood to BMA lab for EIA and WB (if necessary)1

1. AIDSVAX B/E vaccine trial participants, if they choose, may be screened for enrollment in the Bangkok Tenofovir Study. Approximately 50% of vaccine trial participants received the AIDSVAX B/E vaccine, a gp-120 subunit vaccine. In order to ensure that we provide participants with correct information, we will do WB testing on EIA positive specimens to determine if EIA positive results are due to HIV or vaccine.

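### At a reactive visit the risk and adherence questionnaires are listed after the result is disclosed, which leaves seroconverters' self-reports open to differential reporting bias

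*Protocol*

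**What the plan says.** Section 10.3.7 describes what happens when the oral fluid test is reactive. Study medication is stopped. On disclosure, the section says: "the participant will be informed that the test is reactive and that blood tests are required to confirm the result". With the participant's agreement, a sample is then taken for confirmatory testing, "and the participant will complete the risk assessment and adherence questionnaire". Appendix E has the rapid test result given in the clinic on the day of the test: "Give same-day result in clinic".

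Section 10.3.4 counts the HIV infection confirmation visit as an exit visit, where "Clinic staff will conduct all the monthly and 3-monthly procedures". Table 2 marks both ACASI questionnaires at the exit visit, so both are due again with the reactive result already known.

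Otherwise the adherence ACASI is due at every monthly visit (10.3.2) and the risk ACASI at weeks 12, 24, 36 and so on (10.3.3). Neither section, nor Table 2, says whether the questionnaire comes before or after the test result.

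Two passages state the aim for these measures. Section 10.3 gives as one reason for frequent visits: "Reduce recall bias in measures of adherence and HIV associated risk behavior". Section 13.3 names ACASI as a way to limit bias. Section 14.2 requires interim reports to include "Analyses of efficacy outcomes adjusted for medication adherence".

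**The concern.** A seroconverter detected by OraQuick answers questions about missed doses, injecting and sharing when already told that the test is reactive. A participant with a non-reactive test answers either before the result or after reassurance. The reporting condition then differs by outcome, which is the setting for differential misclassification. Knowledge of the result could push reports either way: a participant may look for missed doses that explain the infection, or may claim full adherence to avoid blame. ACASI reduces interviewer effects but does not remove this knowledge.

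The wording can also be read as making the questionnaires depend on agreement to proceed, in which case some reports at this visit may be missing selectively among reactive participants.

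At stake are analyses that set self-reported adherence or behavior against infection. For adherence there are other measures to fall back on (section 9.5). For risk behavior the protocol names no objective check.

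**Working it through.** **Order of steps.** The relevant sections, side by side:

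| Section | What it fixes |
| --- | --- |
| 10.3.7 | Disclosure of the reactive result is mentioned first, then the blood draw and both questionnaires |
| Appendix E | Rapid result on the same day, in clinic |
| 10.3.2, 10.3.3, Table 2 | Which questionnaires are due at which visit; no order relative to the test |
| 10.3.4, Table 2 | Both questionnaires at the confirmation visit, after the reactive result is known |

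No section requires self-report before the result. The only section that mentions both puts disclosure first.

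**Number of participants.** The protocol gives no figure for this point, so only its scale can be worked out. Inputs: 40 endpoints and 2,400 participants (Protocol Summary), 1:1 randomization, and 67% efficacy (13.2). With hazard ratio HR = 1 − 0.67 = 0.33:

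- Tenofovir endpoints = 40 × 0.33 / 1.33 = 9.9
- Placebo endpoints = 40 − 9.9 = 30.1

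This agrees with the 10 and 30 in Table 4. The seroconverters' share of all participants is 40 / 2,400 = 1.7%. The 40 is a ceiling for those affected, because some infections may be found in other ways (see the objection).

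**Effect on a whole-arm adherence comparison.** Assumptions: 1,200 per arm, one report per participant, true adherence 70%, all 40 seroconverters affected, and 30% of the adherent ones reporting non-adherence. The spurious difference between arms is 0.70 × 0.30 × (30 − 10) / 1,200 = 0.0035, or 0.35 percentage points.

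**Effect on a comparison of infected with uninfected participants.** Assume the same true adherence p in both groups, so the true odds ratio is 1. Let a share m misreport among seroconverters only.

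- Under-reporting: p₁ = p(1 − m)
- Over-reporting: p₁ = p + (1 − p)m
- Apparent odds ratio = [p₁/(1 − p₁)] / [p/(1 − p)]

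For p = 0.70 and m = 0.30, under-reporting gives p₁ = 0.49 and (0.49/0.51)/(0.70/0.30) = 0.41. Over-reporting gives p₁ = 0.79 and (0.79/0.21)/(0.70/0.30) = 1.61.

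| p | m | Under-reporting | Over-reporting |
| --- | --- | --- | --- |
| 0.70 | 0.10 | 0.73 | 1.16 |
| 0.70 | 0.20 | 0.55 | 1.36 |
| 0.70 | 0.30 | 0.41 | 1.61 |
| 0.50 | 0.30 | 0.54 | 1.86 |
| 0.85 | 0.30 | 0.26 | 1.50 |

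Both p and m are assumed; the protocol gives neither. The table shows only that modest misreporting confined to cases can distort such an odds ratio in either direction, while arm-level rates stay almost unchanged.

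**The case against.** The strongest reply is that section 10.3.7 is not a strict timetable. The same sentence puts laboratory confirmation ahead of the questionnaires, although that testing is done at the BMA laboratory and its results come at a later visit. The monthly adherence ACASI may already precede the rapid test in practice, with 10.3.7 adding a further form. The study-specific procedures manual mentioned in 14.1, which is not shown, could set the order. This stands in part: the protocol does not prove that no report precedes disclosure. But it then yields two reports from one visit without saying which counts, and the only order it does mention is the unfavorable one.

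Several stronger inferences are tempting and are not supported:

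- *Uninfected participants never report after a reactive result.* Those whose reactive test is not confirmed do. The protocol does not say how many there will be.
- *All 40 infections are affected.* Section 10.3.7 also provides for nucleic acid testing of sera from non-reactive participants, and for testing of earlier specimens. Some infections may be found, or dated, at visits where the participant had been told there was no evidence of infection.
- *The damage cannot be repaired.* Earlier monthly adherence and 12-weekly risk reports exist and can be used. What they miss is the last interval before detection.
- *The adherence endpoint is compromised.* Section 7.2 defines it by interview together with the adherence card, as an overall rate. Section 9.5 adds pill counts, diaries and, for tenofovir recipients only, blood levels. Section 14.2 does not say which measure its adjustment uses.

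It is also fair to say that an extra risk questionnaire at the reactive visit shortens recall compared with waiting for the next scheduled one. Such a form is triggered by the result and must follow it, so re-ordering cannot help there.

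**Conclusion.** The point holds as an avoidable weakness in the order of procedures. As written, the protocol collects self-reports from OraQuick-detected seroconverters with the reactive result known, and nothing secures an uninformed report at that visit. Those reports are open to differential reporting bias. The documents do not show that they are biased, by how much, or in which direction; the odds ratios above rest wholly on assumed misreporting.

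The reach is limited. A reader might infer a threat to the efficacy result. There is none for the primary intention-to-treat analysis, which uses HIV test results, and whole-arm secondary comparisons hardly change. The exposure is confined to analyses relating self-reported adherence or risk behavior to infection, including adherence-adjusted efficacy where it uses self-report. Adherence is partly protected by the other measures; risk behavior is not. The change is worth making because it costs almost nothing and serves the aim stated in section 10.3.

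**What to change.** State in sections 10.3.2, 10.3.3 and 10.3.7 that the scheduled ACASI (adherence at every monthly visit, risk at the 12-weekly visits) is completed before the OraQuick result is disclosed.

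Flag every questionnaire completed after a reactive result as post-disclosure. This includes an off-schedule risk questionnaire at the reactive visit and both questionnaires at the confirmation visit. Use the last pre-disclosure report in comparisons of infected with uninfected participants, and treat the flagged reports as descriptive.

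The cost is a re-ordering within an existing visit and one flag on a form; no procedure is added. There are two downsides. The participant receives the result slightly later in the same visit, and where no risk questionnaire was due, the last pre-disclosure risk report may be up to 12 weeks old.

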**10.3.8. Follow-up visits if tenofovir safety and efficacy demonstrated**

If this study, or other tenofovir studies, determines that tenofovir is safe and effective in preventing HIV infection, HIV seronegative participants will be provided with tenofovir for at least 1 year. BMA clinic staff will be available to provide tenofovir daily to participants.

Monthly visits will include pre- and post-test HIV counseling, HIV risk reduction counseling, a rapid oral HIV test and HIV confirmatory testing if needed, and urine pregnancy test (for female participants). Visits at months 3, 6, 9, and 12 will include all monthly procedures plus a risk behavior questionnaire using ACASI and blood will be collected for laboratory safety testing.

**11. Ethics**

The study will be conducted in accordance with the Declaration of Helsinki, the Code of Federal Regulations, Title 45, Part 46 (45 CFR §46), and local ethical and legal requirements.

The protocol, including informed consent (Thai and English), and other requested documents, and any subsequent modifications, will be reviewed and approved by the ethical review committees responsible for oversight:

- Bangkok Metropolitan Administration
- Thailand Ministry of Public Health
- United States Centers for Disease Control and Prevention

After initial approval, all IRB/ERCs will review the protocol at least annually. The Principal Investigators will provide yearly trial updates to all IRB/ERCs including: the total number of participants enrolled, the number of participants who completed the study, and a line listing of all AE and SAE reports. All Data Safety and Monitoring Board (DSMB) reports will be provided to the IRB/ERCs. In addition, the Principal Investigator will provide a final report of trial results to the IRB/ERCs within three months of study termination or completion.

**11.1 Risks**

There are few anticipated health risks to participation in the trial other than minor discomfort associated with physical examinations and blood specimen collection. Some injection and sexual behavior questions may be embarrassing. There have been reports of decreased bone growth and bone strength in studies of tenofovir in animals and reports of renal injury in humans (please, see section 9.1.3).10, 21-23 A small number of persons randomized to tenofovir may experience changes is bone growth or renal function, but most will not and some persons randomized to placebo may also experience these health events. Participants will be monitored closely for clinical or laboratory evidence of bone or renal abnormalities. Based on previous studies, participants randomized to tenofovir may experience gastrointestinal discomfort (e.g., abdominal pain, nausea, vomiting, diarrhea). It is anticipated that prompt discontinuation of study product should quickly resolve any side effects and that no long-term effects should be experienced by the participants.

Among trial participants who become HIV-infected while on tenofovir there is a risk the virus will develop tenofovir resistance. Studies have shown that tenofovir resistance is uncommon, slow to develop, and low level.10 HIV tests will be performed monthly to limit time HIV infected participants will be on tenofovir monotherapy. Based on anticipated enrollment, expected HIV incidence, and trial data,10 it is unlikely any participants will develop tenofovir resistance. HIV infected participants will be tested for tenofovir resistance.

Participants may believe that study drug will protect them from HIV infection and may increase their HIV-related risk behaviors. Potential participants will be told during the informed consent process that we do not know if tenofovir prevents HIV infection and we will not know who is taking tenofovir. Risk reduction counseling will be provided at enrollment and at monthly follow-up visits (please see section 11.4.3). Analysis of data from the AIDSVAX B/E vaccine trial conducted in the same 17 drug treatment clinics showed that participant HIV-related risk behaviors declined by > 30% during the course of the 36 month study.5

Although study sites will make every effort to protect participant privacy and confidentiality, it is possible that participants’ involvement in the study could become known to others. Participants could face the risk of social harms, such as discrimination resulting from community perception that the individual is at high risk or already infected with HIV. Such discrimination may result in problems such as denial of insurance or employment. These risks will be minimized via thorough education, informed consent, and counseling to give subjects realistic expectations of an experimental medication and to emphasize avoidance of risk behaviors. We will collect details of social harm reports on a social harm report form and will treat reports of social harms as adverse events if they meet clinical AE criteria.

**11.2 Benefits**

Participants in this study will benefit from HIV education and risk reduction counseling and HIV testing. Methadone treatment, contraception, bleach (for cleaning injection equipment), and hepatitis B vaccination will be offered free of charge. Participants and others may benefit in the future from any information learned from this study that may lead to the development of a safe and effective intervention that prevents HIV infection.

